### 2.12. Data collection and management

The principal researcher will be responsible for recruiting participants and applying the data collection instrument. Three nurses will be responsible for applying the intervention in the control and intervention groups, without knowing what will be evaluated.

The participation of patients will be carried out on a voluntary, nonprofit basis and will occur upon reading and signing the Free and Informed Consent Form by the family member, which demonstrates that the individual accepts to participate in the research, explaining all stages, objectives, risks and benefits of the research. It is possible for participants to dropout at any stage of the research without prejudice to treatment and without suffering penalties or judgments of any kind.

The researchers will ensure that the anonymity of participants is protected and their data will remain confidential so that their identities and any type of identity information is protected. Two copies of the consent form will be provided, both signed by a family member and responsible researchers.

The results of this research will be presented at meetings or publications; however, the identity of participants will not be revealed. Original documents and files will be kept at the test sites for 15 years. The principal investigator is responsible for storing data and files and will have access to the final set of data and dissemination.

### 2.13. Management of losses and dropouts

Losses and dropouts will be carefully recorded, ensuring the reliability of the research. If any participant in the sample withdraws from participating in the study, he/she will be removed from collection and another participant will be included.

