### 2.5. Recruitment

The study flowchart is described in Figure 1. Patients will be recruited upon the need for nasoenteral tube insertion the ICU. At the opportunity, the eligibility criteria for participation in the research will be applied. Subsequently, as critical patients admitted to the ICU are unable to consent, consent will be obtained from legal guardians prior to the intervention. Each research participant will have to fill out the Free Informed Consent Form, with the reading and signature of the respective family member legally responsible for the patient.

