### 2.8. Endpoint

#### 1.2.8. Primary outcome.

The success rate on the first attempt will be considered as the dependent variable. Insertion success will be defined as the successful passage of the tube on the first attempt and confirmed by radiography of the correct anatomical positioning of the tube distal tip, which will be performed immediately after the procedure. If the nasally placed small-bowel feeding tube is not successfully inserted, it will be considered a failure and recorded as an unsuccessful attempt. Subsequently, new attempts will be performed.

The number of attempts required for successful insertion will be recorded for each patient. It should be noted that if more than 3 attempts are required, the procedure will be declared unsuccessful and data will be used to count failures. In these cases, the researchers may use another method of free choice for nasally placed small-bowel feeding tube insertion.

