#### 2.2.8. Secondary outcome.

Secondary endpoints will be time required and associated complications. The time required will be recorded from the nasally placed small-bowel feeding tube insertion from the nostril to the calculated length of the tube with the aid of a stopwatch. The insertion times for each attempt will be counted and, in case of failures, the time required for each attempt will be added together.

In addition, AEs associated with the insertion techniques (bleeding of the visible mucosa, nasal mucosa edema, in addition to tube bending, twisting, knotting and insertion into the trachea visible on X-ray) will be recorded. It is noteworthy that the occurrence of bleeding will be considered as visible bleeding in the tube extension and nasal or oral mucosa. The analysis of such AEs will be performed immediately at the end of the procedure until radiological confirmation of the tube positioning and previous removal of the guide wire. The radiograph will be performed on the patient bed and the patient will be kept in the same position, in the supine position. If the patient shows signs of respiratory distress during insertion, the procedure will be stopped.

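### Section 2.13 removes and replaces withdrawn participants with no time limit, so patients withdrawn after allocation drop out of the randomised comparison

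*Protocol article*

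**What the plan says.** Section 2.13 of the protocol article gives the rule for anyone in the sample who withdraws: "he/she will be removed from collection and another participant will be included". The sentence before it promises documentation: "Losses and dropouts will be carefully recorded, ensuring the reliability of the research". Section 2.12 sets no limit on when a participant may leave: "It is possible for participants to dropout at any stage of the research".

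Section 2.5 places consent ahead of the procedure ("consent will be obtained from legal guardians prior to the intervention"), and Table 1 in section 2.11 lists consent under enrollment, ahead of allocation.

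Under Primary outcome in section 2.8, a tube that is not successfully placed is scored as a failed attempt, and "if more than 3 attempts are required, the procedure will be declared unsuccessful and data will be used to count failures". Under Secondary outcome, a safety stop is described: "If the patient shows signs of respiratory distress during insertion, the procedure will be stopped".

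Section 2.6 blinds only the data analysts. The researcher who randomises also times the insertion, completes the form and reads the X-ray.

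**The concern.** Randomisation protects the comparison only if the patients analysed are the patients randomised. A rule that takes a patient out after allocation and puts in someone else breaks that link. If the reason for leaving has anything to do with the assigned technique or with how the first attempt went, the arm's success rate is distorted. If failures are lost preferentially, the distortion favours the arm that loses them.

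Three features of this trial make the rule worth correcting. The outcome is known almost at once, so a withdrawal after the procedure has begun can come when technique and result are already known. The people collecting the data are not blinded. The arms are small, so one patient carries much weight. Section 2.1 says data collection is under way, so the rule may already be in use.

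**Working it through.** **Does the rule reach patients already randomised?**

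1. Section 2.13 applies to any participant in the sample and states no cut-off.
2. Section 2.12 allows withdrawal at any stage.
3. Table 1 puts consent before allocation, so a participant can withdraw either before or after being randomised.
4. No section limits replacement to the time before allocation or says that a withdrawn patient stays in the analysis.

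The rule as written therefore covers withdrawals after allocation. The failure-counting rule in section 2.8 protects failures among patients who remain, but not those of a patient who is withdrawn.

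**Arm size.** Sections 2.9 and 2.10 give 39 patients in three groups. Section 2.9 also states 13 controls and 26 for each intervention group, which would total 13 + 26 + 26 = 65. Only 39/3 = 13 per arm fits the total, so 13 is used here. The total of 39 does not reproduce from the stated effect size of 0.80: three-group ANOVA with f = 0.80 gives 19, and chi-square with 2 df and w = 0.80 gives 16. That is a separate matter, and nothing below depends on it.

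**Weight of one patient.** 1/13 = 7.7 percentage points.

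**Expected shift when one failure is replaced.** The failure contributes 0 successes and the new patient, assumed to enter the same arm, contributes p on average. The shift is p/13.

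- p = 82.7% (86 of 104, the study cited in the Introduction): 0.827/13 = 6.4 points.
- p = 50% (assumed): 0.50/13 = 3.8 points.

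The full 7.7 points applies only if the replacement is certain to succeed. At 82.7%, an arm of 13 expects 13 × 0.173 = 2.2 failures.

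**Systematic loss of failures (illustration).** Suppose two arms of 13 have equal true success p, and a share q of failures in one arm is withdrawn and replaced. Expected observed success in that arm is p/(p + (1 − p)(1 − q)). For example, with p = 0.827 and q = 0.25: 0.827/(0.827 + 0.173 × 0.75) = 86.4%. Type I error comes from exact enumeration of all 13 v 13 tables at the 5% level.

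| p | q | Observed success | Chi-square, uncorrected | Fisher |
|---|---|---|---|---|
| 82.7% | 0 | 82.7% | 3.9% | 1.2% |
| 82.7% | 25% | 86.4% | 4.1% | 1.2% |
| 82.7% | 50% | 90.5% | 5.7% | 1.8% |
| 50% | 0 | 50.0% | 7.6% | 2.9% |
| 50% | 25% | 57.1% | 9.4% | 3.9% |
| 50% | 50% | 66.7% | 17.8% | 8.9% |

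The documents give no withdrawal rate, so every q is an assumption, as is p = 50%. At the cited success rate, the harm is mainly an upward bias in the estimate, and the false-positive rate moves little. Marked inflation needs both a much lower success rate and heavy loss of failures from one arm only.

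**The case against.** The strongest reply is that the route to bias is narrow. Patients are comatose, families consent beforehand, and follow-up ends at an X-ray taken straight after the procedure. Nothing in the article says that relatives watch the attempt or learn its result before the X-ray. Some withdrawals would fall before allocation and do no harm. This stands, and it limits the likely size of the problem. It also means a reader should not infer that withdrawals are likely to be linked to outcome, or that each one hides a probable failure. The article supports the possibility only.

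A reader might also infer that insertions stopped for respiratory distress would be replaced under this rule. The documents do not support that. The stop under Secondary outcome ends the procedure and does not take the patient out of the study, while Primary outcome already scores a tube not successfully placed as a failure. Stopped or incomplete insertions are not part of this point.

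It can be said, too, that removal from collection need not mean discarding data already gathered, that losses will be recorded, and that analysis sets are often left to a statistical analysis plan. The wording is indeed open on data already collected. But filling the place with another participant points to a completed sample of 39 without the withdrawn patient, and recording a loss does not return that patient to the comparison. Because the article states a rule, a plan that kept such patients would have to depart from it.

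**Conclusion.** The point holds as a defect in a stated rule. Section 2.13, read with section 2.12 and Table 1, allows a randomised patient to be dropped and replaced at any time, including after a failed first attempt, so the analysed set can differ from the randomised set. Whether bias follows depends on withdrawals being related to technique or result, which the documents neither show nor exclude.

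The size is 7.7 points per patient with 13 per arm. The expected shift is about 6.4 points for each failure replaced, assuming the cited 82.7% success rate and a replacement in the same arm. How many such withdrawals will occur is unknown, and there may be few. The point should be fixed, because the rule is wrong in principle and cheap to correct. The realistic effect does not justify a higher grade.

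**What to change.** Rewrite section 2.13 as follows:

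- Replace only patients withdrawn before allocation.
- Analyse every randomised patient in the assigned arm, and keep outcome data already collected unless consent to use them is withdrawn.
- Report all withdrawals after allocation by arm and by timing (before any attempt, between attempts, after the last attempt). Include any that have already occurred, since recruitment has started.
- Where the outcome is unavailable, show a sensitivity analysis that counts the patient once as a failure and once as a success, as far as consent permits.

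A patient who had no attempt, or whose family has withdrawn use of the data, should not simply be entered as a failure in the primary analysis. That would bias against the assigned arm or go beyond the consent given.

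The cost is wording only, and the planned 39 need not change. The evaluable number may end slightly below 39. If the sponsor prefers to cover that by recruiting more, 39/(1 − d) gives 42, 44 and 46 for assumed losses of 5%, 10% and 15%. Rounded up to equal arms of 14, 15 and 16, that is 42, 45 and 48.

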### 2.14. Data extraction and statistical analysis

Data will be analyzed using the Statistical Package for Social Science software, version 18.0 (SPSS Version 20.0), where descriptive and inferential analyses will be carried out, and results will be presented through tables, charts and figures. To evaluate variables, the Chi-square test (χ²) or Fisher test or ANOVA will be used. Other statistical tests that may be necessary will also be used. Significance level of 5% (*P* = .05) will be adopted.

### 2.15. Patient and public involvement

All the patient information will be anonymously analyzed and processed. Patients and/or the public were not involved in the design, or conduct, or reporting, or dissemination plans of this research.

## 3. Discussion

The analysis of the effectiveness of different nasoenteral tube insertion techniques in coma (physiological or induced) and intubated patients is initially necessary due to the difficulty of inserting small-bowel feeding tube in a blind manner, with the patient head in the neutral position. The high rate of complications resulting from the small-bowel feeding tube insertion due to the absence of a proven safer method poses a risk to the patient.

A randomized clinical trial emphasizes that the small-bowel feeding tube insertion is often a challenge for ICU professionals. Therefore, the use of instruments that help through visualization was also reported as a facilitator for tube insertion and proper small-bowel feeding tube positioning in critically ill patients, such as laryngoscopes and videolaryngoscopes. Radiological and endoscopic techniques and methods guided by electromagnetism and fluoroscopy will also be used.^[13]^

Therefore, it is important and necessary to offer safer care with less risk of complications based on the best available evidence for the possibility of revealing the most adequate, effective, fast and safe technique to improve the performance of this procedure.

In addition, there is the possibility of characterizing nursing care based on new techniques in order to be used in clinical practice and to expand the knowledge base and skills of nurses in managing the small-bowel feeding tube insertion in critically ill patients, being an accessible and low-cost technology that can be used by nurses, streamlining work processes and contributing to adequate, safe and quality care.

Results favorable to the use of different nasoenteral tube insertion methods have been described by anesthesiologists.^[14–16]^ Among these, the lateralized head^[4,15]^ and the use of the laryngoscope^[4]^ stand out. Such studies have demonstrated small-bowel feeding tube insertion methods that are faster, more effective and that cause less complications to patients.

However, it is clear that such techniques are little used by nurses in clinical practice, in addition to a gap related to the deficiency of experimental studies with high level of evidence in relation to new small-bowel feeding tube insertion techniques to aid decision-making in clinical practice, which justifies the conduction of the present study.
